## Abstract

**Background:**

Non-prescribed anabolic androgenic steroid (AAS) use is associated with AAS-induced hypogonadism (ASIH), and metabolic, cardiovascular, and mental health risks. Symptoms of ASIH (fatigue, depression, anxiety, sexual dysfunction) are hard to endure following cessation, but there is no consensus on whether endocrine treatment should be used to treat ASIH. This proof-of-concept study aims to explore safety of off-label clomiphene citrate therapy, whether the treatment will reduce the symptoms of androgen deficiency, and to study changes in health risks after cessation.

**Methods:**

In this open-labeled non-randomized off-label hormone intervention pilot study, we shall include males with AAS dependence intending to cease use. The 16-week intervention included clomiphene citrate, transdermal testosterone gel for the first four weeks and optional human chorionic gonadotropin (hCG) from week 4 if low treatment response. Measures of physical and mental health will be examined from ongoing AAS use, during the intervention, and at 6- and 12 months post cessation. Change in self-reported symptoms of hypogonadism and other withdrawal symptoms will be compared with data from a group of men who ended AAS use temporarily without the medical intervention. The study may provide valuable clinical insights and may be used to inform the design of future intervention studies.

Specifications table

**Table utbl0001:** 

Subject area:	Medicine and Dentistry
More specific subject area:	Endocrinology, anabolic androgenic steroid induced hypogonadism
Name of your protocol:	Off-label use of Clomiphene citrate to Treat Anabolic-androgenic Steroid induced Hypogonadism upon cessation among men (CloTASH) - a pilot study protocol
Reagents/tools:	Clomiphene citrate, testosterone, human chorionic gonadotropin
Experimental design:	Open label non-randomized off-label hormone intervention study
Trial registration:	EudraCT 2020–005938–15
Ethics:	The research will be carried out according to the Helsinki declaration. The study is approved by the Regional Committee for Medical and Health Research Ethics (REC) in Norway (33872), Norwegian Medicines Agency (21/18081–9) and the Data Protection Officer for Research at Oslo University Hospital (20/27593). All participants will receive oral and written information about the study and written formal consent will be collected.
Value of the Protocol:	• This is the first study to test feasibility of off-label use of clomiphene citrate with the intention to restart endogenous testosterone production upon cessation of anabolic androgenic steroids (AAS) among men with AAS induced hypogonadism. • The study may provide valuable clinical insights, enabling the exploration of whether adjustments are needed for the intervention. • The results may be used to determine the sample size and informing the design of future RCTs or case comparison studies.

## Background

Non-prescribed AAS are predominantly utilized by male recreational athletes in cyclic patterns, with intermittent breaks or continuous administration. Global lifetime prevalence of AAS use among men is estimated to be 6.4 %, but is found higher in subpopulations [1] and associated health risks and behavioral outcomes make AAS use a public health concern [2]. The wide range of adverse effects on mental [3] and physical health [[4], [5], [6]] includes negative effects on the cardiovascular system such as ventricular dysfunction [7], myocardial hypertrophy [8], hypertension [9], severe biventricular cardiomyopathy [10], acute myocardial infarction and sudden cardiac death [8,11]. Increased carotid intima-media thickness, reduced arterial elasticity and lower carotid artery compliance are early predictors of atherosclerosis and cardiovascular risk that are found among men with long term AAS use [12]. AAS use is also associated with altered renal, hepatic and metabolic functions [13]. High androgen levels might lead to gynecomastia and several dermatological conditions, and infertility during ongoing use is common due to the disruption of hypothalamic-pituitary-gonadal (HPG) axis [14,15].

One in three people using AAS seem to develop a dependence syndrome characterized by a pattern of escalating doses and reduced breaks between cycles, or continuous use despite experiencing adverse effects and a desire to cease use [16]. The neuroendocrine mechanism of AAS dependence is linked to suppression of the hypothalamic-pituitary-gonadal (HPG) axis leading to AAS-induced hypogonadism (ASIH) [14]. The features of androgen deficiency (fatigue, depression, anxiety, and sexual dysfunction) will first occur weeks after AAS cessation. The endogenous testosterone production typically recovers after 3–12 months, but this phase is hard to endure [17], often resulting in restart of AAS use.

Despite experiencing health problems associated with AAS use, many individuals fail to receive treatment [18,19]. This reluctance to engage with health services may be attributed to limited treatment options and insufficient awareness of AAS among clinicians. Many individuals who use AAS feel stigmatized, and fear being identified with or labelled as either drug users or sport cheats, with this acting as a further barrier to service engagement [20]. Instead of seeking health services, people who use AAS commonly seek knowledge among peers including in online communities. When AAS use is ceased, some may self-initiate Post Cycle Therapy (PCT) with non-prescribed hormonal substances in various combinations and doses with the intention to restore the HPG-axis faster. As one of few countries, Norway has integrated AAS and other performance and image enhancing drugs (PIEDs) in the National Drug Policy. Possession and use of AAS and other PIEDs became criminalized in 2013, and people with current or previous AAS use got access to SUD treatment in the specialist health service. There is no consensus, nationally or internationally, on whether endocrine treatment should be used in the treatment of ASIH, but endocrinologists have proposed potential interventions [21]. There is a knowledge gap regarding treatment of this patient group, and we describe a non-randomized proof-of-concept study to test a 16 weeks off-label hormone intervention for men who struggle to cease AAS use.

## Description of protocol

### Aims

The primary aim of the present study is to explore whether the 16 weeks therapy model with clomiphene citrate (CC) leads to stimulation of endogenous luteinizing hormone (LH) and testosterone production, if the treatment model is safe, and if the model is more effective in reducing AAS withdrawal symptoms compared to no intervention. The secondary aims are to detect health risks during ongoing AAS use in the intervention group only and assess whether and to what extent the health risks are reduced 12 months after cessation of AAS.

## Methods and analysis

In this open-labeled non-randomized proof-of-concept intervention study, we aim to include 25–30 AAS-dependent men who struggle to cease their AAS use. The subjects in the intervention group will receive 25 mg chlomiphene citrate every second day following AAS cessation for 16 weeks. The comparison group comprise participants in another study of men who ended AAS use temporarily without the intervention and the groups will be compared on self-reported withdrawal symptoms.

### Participants

Inclusion criteria for the intervention group comprise men above 18 years of age with continuous AAS use, AAS dependence, a desire to cease use and previous unsuccessful attempts to cease use. Men with cardiovascular conditions, severe mental health problems or severely reduced liver function will be excluded from the off-label hormone intervention. Men above 18 years of age who use AAS in cycles with breaks in between may be included in the comparison group. For more details about inclusion and exclusion criteria for the intervention group and comparison group, see Table 1.

**Table 1 tbl0001:** Inclusion and exclusion criteria for the intervention group and the comparison group.

	**Intervention group**	**Comparison group**
**Inclusion criteria**		
Age	≥18 years	≥18 years
AAS use	Continuous AAS use ≥6months	Cycle, ≥6weeks between cycles
Dose	Supraphysiological	≥400 mg/week
AAS dependence	3 or more items last 12 months: tolerance, withdrawal, increased amount, unsuccessful efforts to reduce or cease use, ↑time to obtain/use substances, ↓social/recreational/occupational activities due to use, continued AAS use despite mental and/or physical side effects	No
Plan to cease AAS use	Wish to cease use, previous unsuccessful attempts	No
SUD treatment	Being enrolled in or referred to Substance Use Disorder (SUD) treatment	No
Hormonal and liver status at intervention start	Serum testosterone < 25 nmol/l, liver enzymes alanine transaminase (ALT) and aspartate transaminase (AST) < 3 x upper limit of normal range (ULN) (normal range ALT 10–70 U/L, AST 15–45 U/L)	No
**Exclusion criteria**		
Mental health	Previous or current: Severe depression, bipolar disorder, psychosis	Reduced cognitive function (IQ<80) and/or previous or current: Severe depression, bipolar disorder, psychosis. Use of medications that may impact CNS functioning (e.g., antipsychotics, methyl phenidate, TRT)
Physical health	Hypersensitivity to clomiphene citrate, hyperprolactinemia, untreated thyroid or adrenal disease, hemoglobin >18.0 g/dl, current/previous thromboembolic disease, cardiovascular disease (arrhythmia, ischemic heart conditions, heart failure)	Traumatic brain injury with consciousness >1 min, or neurological disorders (e.g., multiple sclerosis, ischemia) or severe somatic disorders (e.g. cancer)
Substance use	No illicit substance use during intervention, <8 alcohol units/week	Problematic use of alcohol or illegal substances (evaluated with Alcohol Use Disorders Identification Test and Drug Use Disorders Identification Test C)

Recruitment for the intervention group**:** The National Steroid Project at Oslo University Hospital (OUH) will recruit participants for the intervention study through a national information service [24], the outpatient SUD clinic at OUH, flyers in various gyms and through advertisements on social media; Facebook, Instagram, TikTok, Snapchat and AAS user forum.

Recruitment for the comparison group**:** Advertisements on social media.

### Study design

The study includes two sub-studies with

A) *Within-subjects repeated measures design* to monitor the intervention group with physical and mental health parameters and blood sampling prior to intervention start and while still using AAS, during 16 weeks of intervention, and at follow-up at 6 and 12 months (Table 2).

**Table 2 tbl0002:** Flow chart of study events during the study period for the intervention group, modified version of SPIRIT.

B) *Single center – single group – case-comparison design*:

Male participants with AAS dependence and continuous AAS use with the intention to cease use permanently comprise the intervention group. The data from the intervention group will be compared with data from an ongoing study of men who intend to cease a cycle of AAS use temporarily without receiving intervention. Participants from both studies will self-report withdrawal symptoms and other subjective health measures during ongoing use and after cessation. The intervention group will self-report withdrawal symptoms every 2 weeks for 16 weeks of intervention, see Fig. 1.

**Fig. 1 fig0001:**
[figure not shown]
Timeline for data collection for the intervention group and the comparison group.

### The intervention

Rahnema and colleagues presented a treatment model to prevent severe symptoms of hypogonadism during cessation of AAS including use of CC, a Selective Estrogen Receptor Modulator (SERM), to restart the HPG-axis [14]. CC selectively binds to estrogen receptors and acts as a receptor antagonist with week estrogen activity in the hypothalamus which leads to blocked negative feedback inhibition. This leads to increased gonadotropin-releasing hormone (GnRH) pulsation in the hypothalamus, increased release of luteinizing hormone (LH) from the pituitary gland and finally increased levels of endogenous testicular testosterone. CC is approved for short-term treatment of female infertility. CC as off-label treatment has been found safe, tolerable and effective to improve serum levels of testosterone, symptoms of hypogonadism and infertility in men with hypogonadism of other causes than AAS use [22,23]. In the reviewed studies, dosages of 25 mg daily for up to 12 months, 50 mg daily for up to 6 months, and 25–50 mg every second day for 1, 2 and 3 years or more were administered. The majority of these investigations reported no occurrence of major side effects. Side effects reported were: headache, dizziness, mood changes, blurred vision/visual change, breast tenderness/gynecomastia, secondary polycythemia without need for phlebotomy and a few cases of elevated liver enzymes [22,23].

This protocol involves a slightly modified version of the 16 week therapy model outlined by Rahnema and colleagues involves administration of 25 mg CC orally every second day for 16 weeks [11]. Testosterone 50 mg is given transdermal daily for the first 4 weeks as rescue medication before the expected endogenous Testosterone (T) response, see Fig. 2. The target T level during the intervention is set at 20 nmol/l. If the endogenous LH and T response is poor (T < 10 nmol/l) after 4 weeks, human chorionic gonadotropin (hCG) will be added as 1500 IE subcutaneous injection twice a week, as rescue medication. If the endogenous T response is still poor after 8 weeks, the same dose will be given three times a week for four more weeks or throughout the intervention. If poor response on endogenous LH and T levels below lower limit of normal range after 16 weeks intervention *and* the participant experiences severe symptoms of hypogonadism; testosterone replacement therapy (TRT) and referral to endocrinologist will be considered.

**Fig. 2 fig0002:**
[figure not shown]
The 16 week off-label intervention with clomiphene citrate, testosterone and optional hCG *human chorionic gonadotropin.

### Outcomes and instruments

Primary outcomes:(1)*Changes in self-reported symptoms of hypogonadism,* mental health state, and symptoms associated with AAS use. The following will be assessed for both the intervention and comparison group: fatigue, depression, suicidal ideation, anxiety, wellbeing, sexual dysfunction, sleep quality, aggression, and body dysmorphia.(2)*Side effects related to CC* will be specifically evaluated for the intervention group.

Secondary outcomes:

Change in measures of physical health from baseline to follow-up for the intervention group:•Weight, body mass index (BMI), degree of striae, acne, androgen alopecia and gynecomastia•Endocrine status, metabolic status, liver and kidney function (blood tests)•Cardiovascular status: Blood pressure, electrocardiogram (ECG), vascular morphology (carotid intima-media thickness and pulse wave velocity) and -function (flow-mediated dilation and carotid artery reactivity)•Body composition; total fat mass, visceral and subcutaneous fat tissue, total lean mass, and bone mineral density•Testicular volume and sperm quality•Immunological biomarkers, analyzed from biobanked blood and adipose tissue samples

Change in measures of mental health risks from baseline to follow-up after 12 months:•Depression and anxiety levels, AAS dependence, body image concerns, aggression, AAS use, and adherence to SUD treatment

Study participants included for the intervention will be screened for eligibility at baseline and examined to assess mental health status, comorbidity, AAS history, AAS dependence and SUDs with validated instruments, see flow chart for study events (Table 1).

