#### Self-reported mental health, well-being and AAS withdrawal symptoms

To investigate mental health state, wellbeing and AAS-withdrawal symptoms after AAS cessation, the following self-reporting questionnaires will be administered via a web-app every second week for 16 weeks for both groups and at follow-up at 6 and 12 months for the intervention group: Hopkins Symptom Checklist-10 (HSCL-10) to evaluate psychological distress, suicidal ideation item from Montgomery and Åsberg Rating Scale (MADRS), items from Health-related quality of life (HRQOL) to evaluate sexual function, Shortened Fatigue Questionnaire, WHO-5 Wellbeing Index and Jenkins Sleep Scale (JSS), Body Perception Questionnaire; and Visual Analog Scale (VAS) to measure aggression, cognitive function, body image and pain. Treatment satisfaction will be assessed using VAS for the intervention group only.

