### Data analysis plan

Data analyses will follow a full analysis set, with a per protocol plan. Descriptive statistics will be used when appropriate and for reported adverse events. For between-group comparisons and to control for the effect of baseline characteristics, we plan to use General Linear Mixed Models (GLMM) with a within subject repeated measures design at baseline, 6 months and 12 months. In cases where the outcomes do not meet the normality assumption, we will apply a General Alinear Mixed Models (GAMM) approach. The results of statistical analyses will be performed using 95 % CIs, and a two-sided P value of < 0.05 will be used to indicate statistical significance. General linear models may be utilized in cases where GLMM/GAMM is considered inappropriate. Two sample *t*-tests will be used for between-group comparisons of numerical variables, when we see no need to adjust for confounding variables. Numerical data not following normal distribution will be presented as medians (25th-75th percentiles), using non-parametric tests such as the Wilcoxon rank sum tests (Mann-Whitney) to compare differences between groups. Chi^2^-tests and Fischer's exact will be applied for categorical variables. Per protocol analysis will be applied in cases of missing data to detect any discrepancy that might affect the robustness of the results. All statistical calculations and analyses will be conducted using up-to-date versions of the statistical software STATA and SPSS.

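### Nine symptom domains are jointly primary under one 0.05 threshold with no lead domain or time point, so the chance of at least one false positive rises from 5% to as much as 37% (about 20% in the direction of benefit)

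*Protocol article*

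**What the plan says.** Under Outcomes and instruments, primary outcome (1) is change in self-reported symptoms, assessed in both groups across "fatigue, depression, suicidal ideation, anxiety, wellbeing, sexual dysfunction, sleep quality, aggression, and body dysmorphia". That is nine domains, with no lead domain, composite or order of testing. Primary outcome (2), side effects of clomiphene, concerns the intervention group only. The section on the scientific rationale again treats the symptom list as the primary endpoints.

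The Aims section makes a comparison part of the primary aim: "if the model is more effective in reducing AAS withdrawal symptoms compared to no intervention".

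The Data analysis plan gives one decision rule for all analyses: "a two-sided P value of < 0.05 will be used to indicate statistical significance". It mentions no adjustment or priority among the domains. It also does not spell the rule out domain by domain.

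On timing, the section on self-reported mental health says the questionnaires are given "every second week for 16 weeks for both groups and at follow-up at 6 and 12 months for the intervention group". The Data analysis plan sets the between-group mixed model as a "within subject repeated measures design at baseline, 6 months and 12 months". Neither section names a primary time point.

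**The concern.** A primary aim of superiority needs a test that can fail. Here the claim could rest on whichever of nine domains gives P < 0.05, and nothing in the article says which one counts. The nominal 5% error rate then does not apply to the claim as a whole.

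The timing makes this worse. A reader cannot fall back on a default contrast, because the between-group model uses 6 and 12 months, when only the intervention group is due to complete the questionnaires.

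There is a second consequence. The article says its results may be used to size later trials. If the domain with the largest observed difference is the one carried forward, the effect size taken from it will be too large on average.

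**Working it through.** **Inputs from the article.** Nine domains (Outcomes and instruments); two-sided alpha of 0.05 (Data analysis plan); a total of 52 participants and a target of 25–30 per group (Sample size determination). I use 52/2 = 26 per group.

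**Assumption.** The article gives no correlation between domains. I use 0, 0.5 and 0.7 as a range.

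**The plan's own figure.** The article states no family-wise error rate, so there is none to reproduce. Its nearest figure is the total of 52 for 80% power at d = 0.4. A two-group comparison at d = 0.4 needs 99 per group, or 198 in total. A total of 52 fits a two-group comparison at d of about 0.8. That is a separate matter, but it is why power is shown below at both effect sizes.

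**Step 1: one test per domain, independent domains.**
- Either direction: 1 − 0.95^9 = 1 − 0.630 = 0.370.
- Direction of benefit only (0.025 per test): 1 − 0.975^9 = 1 − 0.796 = 0.204.

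**Step 2: correlated domains.** Simulating 200,000 sets of nine equally correlated normal test statistics with no true effect gives:

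| Correlation | Either direction | Benefit only |
|---|---|---|
| 0 | 37% | 20% |
| 0.5 | 27% | 13% |
| 0.7 | 20% | 10% |

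**Step 3: is nine the right count?** Depression and anxiety appear to share one instrument, the "Hopkins Symptom Checklist-10 (HSCL-10) to evaluate psychological distress". If they are tested as one score, there are eight tests: 1 − 0.95^8 = 33.7% in either direction and 1 − 0.975^8 = 18.3% for benefit. The conclusion does not depend on this.

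**Step 4: picking the largest effect.** At 26 per group, the standard error of d is about √(2/26) = 0.277. The expected maximum of nine independent standard normal values is 1.485. With no true effect, the largest observed d in the direction of benefit therefore averages 1.485 × 0.277 = 0.41. At correlation 0.5 it averages 0.41 × √0.5 = 0.29. Chance alone could thus come close to the d = 0.4 that the article hopes to detect.

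**Step 5: what adjustment would cost.** Bonferroni uses 0.05/9 = 0.0056 per test and brings the independent family-wise rate to 1 − (1 − 0.0056)^9 = 4.9%. Under the normal approximation, power at 26 per group is Φ(d√13 − 2.773):
- d = 0.8: Φ(2.884 − 2.773) = 54%.
- d = 0.4: Φ(1.442 − 2.773) = 9%.

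**The case against.** **The study is exploratory.** It is an open, non-randomised proof-of-concept pilot whose primary aim is worded as exploring, and family-wise control is not a settled requirement in such a study. This stands as a limit on severity, and it argues for estimation over formal adjustment. It does not remove the point. The article sets a significance threshold, gives a power statement for a single effect size, puts superiority over no intervention into the primary aim and intends to inform later trials.

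**A full protocol or SAP may settle it.** An unseen document may set a hierarchy or an adjustment, and the absence of an adjustment method from a condensed article would not be a finding. But designating the primary outcome belongs in the protocol, and this article does so: it names nine, unranked.

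**The stronger reading.** A reader might infer that a false claim of benefit is likely, or that all nine domains will be tested at each of the eight biweekly visits. The documents support neither. With one test per domain, the benefit rate is about 20% or less. Testing 9 × 8 = 72 times would raise it to 83.8% if independent, 48% with correlations of 0.5 between domains and between times, and 30% with both at 0.7. However, the Data analysis plan describes a repeated-measures mixed model, not visit-by-visit tests.

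**The remedy leaves the main biases.** This is true. A single primary scale does nothing about unblinded self-report or about the group differences that the article itself acknowledges.

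**Conclusion.** The point holds in a limited form. Nine domains are jointly primary under one threshold, with no lead domain and no primary time point, while the primary aim carries a between-group efficacy claim. With one test per domain, the chance of at least one false positive rises from 5% to between about 20% and 37% in either direction. For benefit it rises from 2.5% to between about 10% and 20%. These ranges rest on assumed correlations from 0.7 down to 0 and on reading the general threshold as applying to each domain. The rates would be higher only if time points were also tested separately, which is not planned. The protocol should be changed here, but given the exploratory aim the defect is not fatal.

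**What to change.** 1. In Outcomes and instruments, name one scale already in the web app as the primary symptom outcome, chosen with the user panel.
2. In the Data analysis plan, name one between-group contrast within the biweekly data that both groups supply over 16 weeks.
3. Amend the between-group model to include those visits. As written, it covers baseline, 6 and 12 months and cannot produce such a contrast. The 6- and 12-month data can remain for the within-group analysis of the intervention group.
4. Make the other domains secondary or exploratory, reported as estimates with 95% CIs and no claim of significance.

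If all nine must stay primary, Holm across them would control the error rate. It is less attractive in a sample this small because it also costs power, as the Bonferroni figures above indicate.

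The cost is a sentence in the outcomes and a rewritten model specification, with no new data and no change to treatment. The downside is that fewer results can be called significant. Bias from open-label self-report and from non-comparable groups remains and should still be stated as a limitation.

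### Primary outcome (2) relies on an open-label relatedness label in treated men only, which cannot reliably assign mood changes, gynecomastia and raised liver enzymes to clomiphene

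*Protocol article*

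**What the plan says.** Under Aims in the Protocol article, safety of the treatment model is part of the primary aim. The outcome that serves it, primary outcome (2) under Outcomes and instruments, reads "Side effects related to CC* will be specifically evaluated for the intervention group". Primary outcome (1), by contrast, covers depression, anxiety, suicidal ideation and other symptoms in both groups.

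The intervention section lists the clomiphene effects found in earlier studies: "headache, dizziness, mood changes, blurred vision/visual change, breast tenderness/gynecomastia, secondary polycythemia without need for phlebotomy and a few cases of elevated liver enzymes". It also gives transdermal testosterone in the first four weeks and makes hCG available from week 4.

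The Background gives other sources for some of these effects:
- Breast changes: "High androgen levels might lead to gynecomastia and several dermatological conditions".
- Liver: "AAS use is also associated with altered renal, hepatic and metabolic functions".
- Mood: "The features of androgen deficiency (fatigue, depression, anxiety, and sexual dysfunction) will first occur weeks after AAS cessation".

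Table 1 admits men whose ALT and AST are "< 3 x upper limit of normal range (ULN"), so values above normal are possible before the first dose. Registration of adverse events grades events by CTCAE at four-weekly examinations and registers those at level 2 or above. The Data analysis plan summarises adverse events descriptively.

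**The concern.** The outcome has a causal judgement built into its definition, and that judgement is made without blinding in the treated group alone. For some effects the protocol itself expects the same event from another cause in the same men. Mood is the clearest case. Clomiphene starts after AAS cessation and runs for 16 weeks, and the protocol expects depression and anxiety to appear weeks after cessation. The same worsening can be read as withdrawal under outcome (1) or as a drug effect under outcome (2).

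At stake is the safety statement for these effects. A clomiphene effect on mood could be put down to withdrawal and left out of outcome (2), or withdrawal and residual AAS effects could be put down to clomiphene. The results are meant to inform later trials, so either error would carry forward. Limitations says that the comparison group may have less serious use and fewer symptoms, but does not extend the caution to attribution of side effects.

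**Working it through.** The plan states no event rate, threshold or sample size for this outcome, so there is no figure to reproduce. The check sets the listed clomiphene effects against the other sources that the document names and the reference data that it collects.

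| Listed clomiphene effect | Other source named in Background | Reference data in the plan |
|---|---|---|
| Mood changes | AAS cessation | Two-weekly questionnaires for 16 weeks, both groups |
| Breast tenderness/gynecomastia | AAS use (high androgen levels) | Own baseline only |
| Raised liver enzymes | AAS use | Own baseline, bloods every 4 weeks |
| Headache | None stated | Four-weekly adverse event review |
| Dizziness | None stated | Four-weekly adverse event review |
| Visual change | None stated | Eye examination at inclusion and after the intervention |
| Polycythemia | None stated | Own baseline, blood tests |

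**Extent.** 3 of 7 listed effects overlap by the protocol's own text, and 4 of 7 do not. For gynecomastia and liver enzymes the named source is AAS use. Only for mood is it cessation.

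**Liver values at entry.** Table 1 gives upper normal limits of 70 U/L (ALT) and 45 U/L (AST). The entry ceilings are 3 × 70 = 210 U/L and 3 × 45 = 135 U/L. A man can therefore start with ALT between 70 and 210 U/L, and a raised value during treatment means little unless set against his own starting value.

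**Use of the mood data.** The self-report section collects questionnaires from both groups every second week for 16 weeks, and at 6 and 12 months from the intervention group only. The between-group model in the Data analysis plan is set at baseline, 6 months and 12 months. As stated, that model does not use the two-group data from the treatment window, where drug effect and withdrawal coincide.

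**How much a mood contrast could show.** The rates here are assumptions, because the document gives none. With n per group, proportions p0 and p1, mean proportion m and two-sided 0.05, power = Φ{[(p1 − p0) − 1.96·√(2m(1−m)/n)] / √[(p0(1−p0) + p1(1−p1))/n]}.
- 20% v 40%, n = 25: (0.20 − 1.96 × 0.1296)/0.1265 = −0.43, power 34%. With n = 30, power 39%.
- 20% v 50%: power 61% (n = 25) to 69% (n = 30).

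The comparison group can supply a background rate for mood worsening, but only weak inference, even before the lack of randomisation is considered.

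**The case against.** The strongest reply is that most of the needed data are already planned and that events are not lost. Level 2 or higher events are registered with no attribution filter. Depression, anxiety and suicidal ideation are primary outcomes in both groups. Gynecomastia and liver function are measured before treatment and reported as change from baseline. Vision is examined before and after. The rules for judging causality may sit in the full protocol, which a journal article need not repeat. An open-label, non-randomised pilot cannot settle causation in any case, and the authors acknowledge that an RCT is the gold standard.

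Much of this stands. The data exist, and the absence of a causality procedure from the article is not a finding. It does not rescue the definition of outcome (2), which restricts the reported safety result to events judged related to clomiphene in treated men. A fuller causality procedure would still ask an unblinded assessor to separate causes that are expected in the same men and, for mood, in the same weeks.

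Two stronger readings are tempting, and the document supports neither.
- A reader might infer that the outcome would turn positive even with a harmless drug, and might calculate the chance of at least one background event. The plan has no rule by which one event makes the treatment unsafe, and it gives no background rates. Such a calculation would also ignore the relatedness filter that is the actual problem.
- A reader might infer that the whole outcome cannot separate drug harm from withdrawal. That fails for the four effects with no stated overlap. For liver and breast findings the named source is AAS use, and a within-person baseline exists.

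**Conclusion.** The point holds for mood changes, gynecomastia and raised liver enzymes, three of the seven listed effects. For these, a relatedness label given without blinding in treated men only, with testosterone gel and optional hCG as further candidate causes, cannot reliably assign events to clomiphene. Headache, dizziness, visual change and polycythemia are outside the point.

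The number of events that would be misassigned cannot be estimated from the document. The conclusion rests on the protocol's own account of AAS and cessation effects and on the stated wording of outcome (2), not on any assumed rate. It is a modest defect of definition that is cheap to correct, and it does not invalidate the safety data being collected.

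**What to change.** 1. Define primary outcome (2) as events that are new or worse than the man's own value at intervention start, regardless of attribution. Report relatedness to clomiphene only as a supplementary description.
2. Tabulate mood changes, gynecomastia and liver enzymes separately from headache, dizziness, visual change and polycythemia.
3. Show the proportion of men whose mood or suicidal ideation worsens over the 16 weeks, treated men beside comparison men, from the two-weekly questionnaires already collected in both groups.
4. State the limits: the mood contrast is non-randomised and only a rough reference, liver and breast events have a within-person baseline but no comparison group, and the reported rates will include background events.

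The cost is a rewording of the outcome and one or two tables from data already planned, with no new visits or participants. The drawback is that counting events whatever their cause raises the reported rates, so the fourth item has to accompany the first.
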